#### Long-term follow-up

Six months after the intervention visit, the patient’s medical record will be reviewed to obtain the patient’s most recent laboratory values to examine whether the “red flag” outcome identified in the pre-visit session improved since the coaching session.

### Ethics

The research protocol has been approved by the University of California Irvine Institutional Review Board (HS#2014-1441).

### Inclusion criteria for patients

Patients will be recruited from the UC Irvine Federally Qualified Health Center family medicine clinic sites in Santa Ana and Anaheim with the following inclusion criteria: (1) age 18 and older; (2) have poorly controlled type 2 diabetes (as indicated by HbA1c >7.5%, LDL cholesterol >100 mg/dl or systolic blood pressure >140), (3) be of Hispanic ethnicity and (4) speak English or Spanish.

### Outcome assessments

Study endpoints will be assessed from (1) analysis of audio recordings of the patient’s medical visit with the doctor, (2) the Encounter Form used to document the topics discussed in the Pre- and Post-Visit Coaching Sessions, (3) a brief 2-week follow-up phone call documented in a “Phone Note,” (4) a brief Post-Visit survey and (5) abstraction of laboratory and blood pressure data (HbA1c, LDL cholesterol and blood pressure) from the electronic medical record at 6-month follow-up. Participant characteristics, barriers to access and baseline medication nonadherence will also be assessed with (6) a brief baseline survey. Study outcome assessments are summarized in Figure 5.

**Figure 5 Fig5:**
[figure not shown]
**Data collection overview.**

*Primary Outcomes.* Two primary outcomes will be evaluated for this study.Development of a contextualized plan of care will be assessed by analyzing an audio recording of the medical visit using a previously developed coding scheme [35] (see “Analysis of Audio Recordings”). If the coder concludes that the plan of care discussed in the visit adequately addresses a contextual factor raised during the visit, it will be determined that a contextualized plan of care was developed.Attainment of a concrete behavioral goal will be assessed in a 2-week follow-up phone call to the patient and will be defined as the patient reporting having completed the specific action that he or she specified with the Coach as a concrete goal during the intervention post-visit.

*Secondary Outcomes:* Two secondary outcomes will be assessed.Discussion of a contextual factor in the visit will be assessed from audio recordings of the visit using a previously developed coding scheme [35]. If the coder concludes that a relevant barrier to the patient taking his or her medication consistently was raised during the visit, it will be determined that a contextual factor was discussed.Improvement in “red flag” outcomes will be assessed from the patient’s medical record as the change in the measured value of the outcome measure identified as a high priority outcome (“red flag”) from the intervention visit date till the next regularly scheduled assessment. The red flag outcome measure is selected by the Coach and patient during the intervention visit and can be either hemoglobin A1c, LDL cholesterol or blood pressure level.

#### Additional measures

Several measures of feasibility, acceptability and usability will be collected to describe the participants’ experience with the software tools and the intervention. The measures include: the time required to complete the intervention sessions, the patients’ ratings of the ease of use of the EMPATHy toolkit, confidence to raise the contextual factor with the doctor, relevance of contextual factors discussed, the helpfulness of the doctor’s responses, the relevance of the concrete goals during the intervention visit and confidence that outcomes will improve.

Patient-reported medication adherence will also be assessed using an 11-item self-report measure of patients’ deviations from the prescribed regimen in the face of specific barriers [15,34,43]. This measure has been used in this patient population, is highly correlated with blood sugar control and LDL cholesterol, and captures both the extent of nonadherence and reasons for nonadherence. Additionally, primary nonadherence (failure to fill a prescription) will be collected from patient report during the 2-week follow-up call.

#### Analysis of audio recordings

Audio recordings of the medical visits will be coded by members of the research team using a validated method known as Content Coding for Contextualization of Care (4C) [35,44] (see Figure 6). The coding method involves identifying (1) “red flags” or health issues that warrant discussion of barriers to disease management, (2) whether a “probe” from the doctor asking about barriers that may have contributed to the red flag occurred, (3) whether a “contextual factor” or specific barrier was raised by the patients, and (4) whether a “contextualized plan of care” was created to address the barrier raised. Inter-rater reliability will be evaluated by having each recording coded by two separate coders, and then any disagreement between the raters will be resolved by the lead researcher. Prior studies using the 4C method have reliably identified how frequently contextual factors are discussed [27] and shown that patients who received a contextualized plan of care experience improved outcomes compared to those did not [24].

**Figure 6 Fig6:**
[figure not shown]
**Overview of coding method, Content Coding for Contextualization of Care (4C).**

### Statistical analysis

Participant characteristics, including age, gender, education, type of medical insurance, nativity and employment status, will be compared between groups using univariate statistics. Primary and secondary outcomes are all dichotomous (yes or no) outcomes and will be compared between groups using logistic regression models. Feasibility, usability and patient-reported barriers to nonadherence will be presented descriptively.

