### Objectives

The primary objective of this project is to pilot test “EMPATHy,” a prototype software-based toolkit in a previously developed CHW-led intervention (Coached Care) that is ongoing at the study site with a highly vulnerable population—low-income Mexican-American patients with diabetes and a history of nonadherence. Results from this pilot study will be used to estimate the key parameters necessary to design a definitive trial and ascertain the feasibility and usability of the EMPATHy toolkit.

All study comparisons will be between patients randomly allocated to a “Coached Care + EMPATHy” group versus those assigned to a control group (“Routine Coached Care” with no software).

The specific aims of the project are:*Aim 1.* Evaluate the preliminary impact—after a single intervention visit—of EMPATHy on doctor-patient communication about problems patients are facing with their medication regimens. We hypothesize that compared to controls, patients in the “Coached Care + EMPATHy” condition will:1.1 Be more likely to raise a relevant “contextual factor” (i.e., a barrier to medication adherence in daily life) with the doctor, determined using a validated audio coding scheme [35] to analyze an audio recording of the medical visit.1.2 Be more likely to leave the medical visit with a “contextualized plan of care” (i.e., a plan of care that addresses the contextual factor raised during the visit), determined using the same audio coding scheme.*Aim 2.* Evaluate the impact of EMPATHy on patient follow-through with the plan of care developed during the medical visit with the doctor. We hypothesize that compared to controls, patients in the “Coached Care + EMPATHy” condition will:2.1 At 2-week follow-up, be more likely to have attained a concrete behavioral goal identified during the intervention visit.2.2 By the next regularly scheduled medical visit, be more likely to show improvement in the “red flag” health outcome (A1c, LDL or blood pressure) identified during the intervention visit.*Aim 3.* Assess and describe the feasibility, acceptability and usability of EMPATHy.

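### The secondary red-flag outcome is a measured change in one section and yes/no in others, and is timed by two different rules; one definition, one time window and a matching model are needed

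*Protocol article*

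**What the plan says.** The red-flag outcome is one of two secondary outcomes. The marker is HbA1c, LDL cholesterol or blood pressure, chosen for each patient at the intervention visit. Five places in the protocol article bear on it.

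- **Objectives, hypothesis 2.2:** patients in the software arm should more often show improvement, "By the next regularly scheduled medical visit".
- **Long-term follow-up:** "Six months after the intervention visit, the patient’s medical record will be reviewed to obtain the patient’s most recent laboratory values", in order to see whether the flagged outcome got better after the coaching session.
- **Outcome assessments, opening paragraph:** laboratory and blood pressure data are abstracted "from the electronic medical record at 6-month follow-up".
- **Secondary Outcomes (under Data collection overview):** improvement is assessed "as the change in the measured value of the outcome measure identified as a high priority outcome", running "from the intervention visit date till the next regularly scheduled assessment".
- **Statistical analysis:** "Primary and secondary outcomes are all dichotomous (yes or no) outcomes and will be compared between groups using logistic regression models".

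None of these places says how large a change counts as improvement, or which value to use if a patient has several after the visit, or none.

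**The concern.** Two things have to be fixed before an endpoint can be analysed: what the variable is, and when it is measured. The article gives two answers to each.

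On type, a change in a measured value is not a yes/no variable. Logistic regression cannot be fitted to it without a rule that turns the change into improved or not improved, and the article states no such rule. A threshold alone could reasonably be left to an analysis plan. Here two sections describe different variables, so an analysis plan that agrees with one must contradict the other.

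On timing, the next scheduled assessment and the latest value on file at six months are different selection rules. With both in print, the choice could be made once the data are known.

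At stake is the trial's only clinical health outcome, in a pilot whose stated purpose includes supplying parameters for a definitive trial. A parameter estimated under an unsettled definition is hard to carry forward.

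**Working it through.** **1. The sections side by side**

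| Section | Type of variable | Time of measurement |
|---|---|---|
| Objectives, 2.2 | yes/no (more likely to improve) | next scheduled medical visit |
| Long-term follow-up | yes/no (whether it improved) | latest value at the 6-month record review |
| Outcome assessments, opening | not stated (values abstracted) | 6 months |
| Secondary Outcomes | change in measured value | next scheduled assessment |
| Statistical analysis | yes/no, logistic regression | not stated |

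On type, three places are yes/no and one is a measured change. On timing, two places use the next scheduled visit or assessment and two use six months.

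**2. When the timing rules disagree**

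- One post-visit value within six months: both rules select it.
- Several post-visit values within six months: the next-assessment rule takes the first and the latest-value rule takes the last. These are different measurements.
- First post-visit value later than six months: the next-assessment rule points to it, but the six-month review does not find it.
- No post-visit value: neither rule says what to do.

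**3. The plan's own sample size**

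Inputs from the Sample size section: 40% v 60%, 80% power, alpha 0.05 (two-sided assumed). Unpooled two-proportion formula:

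n per arm = (1.960 + 0.842)² × (0.4×0.6 + 0.6×0.4) / 0.2² = 7.849 × 0.48 / 0.04 = 94.2, so 95 per arm and 190 in total.

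The stated figure reproduces (the pooled-variance form gives 97 per arm, 194). It concerns the primary outcomes. The article gives no calculation for the red-flag outcome.

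**4. What a yes/no split costs**

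Assumptions, none of them in the article: normally distributed change, equal SDs, complete data, one common scale. If a proportion p is classed as improved, the efficiency of the yes/no comparison relative to the comparison of means is φ(z_p)² / [p(1 − p)].

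| Proportion improved | Relative efficiency | Information lost |
|---|---|---|
| 50% | 0.159 / 0.25 = 0.64 | 36% |
| 40% or 60% | 0.149 / 0.24 = 0.62 | 38% |
| 30% or 70% | 0.121 / 0.21 = 0.58 | 42% |
| 20% or 80% | 0.078 / 0.16 = 0.49 | 51% |

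Power at 95 per arm, for a standardised difference d in the change and a control improvement rate of 30% to 70%:

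| d | Measured change | Yes/no |
|---|---|---|
| 0.3 | 54% | 33-37% |
| 0.4 | 79% | 51-59% |
| 0.5 | 93% | 68-78% |

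For reference, 40% v 60% improving corresponds to d = 0.253 + 0.253 = 0.507. At 95 per arm the power is then 79% for yes/no and 94% for the measured change; 80% power needs 97 and 62 per arm respectively.

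**The case against.** The strongest reply is that the yes/no reading is the dominant one. The hypothesis, the follow-up procedure and the analysis section all point that way, and the Secondary Outcomes item itself is labelled as improvement. On this view the logistic model is right and a single clause is loosely worded. That is plausible, and it means the planned model should not be called wrong. The clause still has to change, and a criterion for improvement still has to be stated.

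A second reply is that a common yes/no outcome is a legitimate way to combine three markers in different units. This also stands. Raw changes cannot be pooled, and a pooled standardised analysis treats one SD of HbA1c, LDL and blood pressure as exchangeable. That is a reason to keep such an analysis supportive and not to impose it as the replacement.

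On timing, six months may only be the date of abstraction, with the Secondary Outcomes text deciding which value counts. That is possible, but Long-term follow-up asks for the latest value, so the ambiguity remains whenever there are several.

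Three stronger readings are tempting and are not supported:

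- **That a pre-visit value could serve as the outcome.** Taken literally, the latest value on file could predate the visit. But Long-term follow-up asks about improvement after the coaching session, and the Secondary Outcomes text measures change from the visit date. Both imply a later value; only an explicit rule for no later value is absent.
- **That any decrease counts as improvement.** The article does not say so.
- **That regression to the mean undermines the comparison.** Eligibility requires a raised marker, so falls are expected in both arms. Randomisation makes this equal in expectation. It can push improvement rates up and lower sensitivity, but it does not bias the comparison.

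**Conclusion.** The inconsistency is real on both counts and goes beyond detail that an article may leave out, because the sections cannot all be followed. It should be fixed, but it is not critical: the outcome is secondary, the study is a pilot, and neither the two primary analyses nor N = 190 depends on it.

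The information loss of about 36-51% supports also reporting the measured change. It does not show that the planned analysis is invalid. It rests on normality, complete data and improvement rates between 20% and 80%, all assumed, and the real gain across three markers taken from routine records may be smaller. The power figures depend further on an assumed effect and on its scale. For example, if patients were selected at more than 0.5 population SD above the mean, their baseline SD would be about 0.52 of the population SD, and a benefit of 0.35 population SD would be 0.35 / 0.52, or about 0.68, of the enrolled patients' baseline SD. The power figures should therefore be read as illustration only.

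**What to change.** 1. **One time rule**, used in the Objectives, Long-term follow-up, Outcome assessments and Secondary Outcomes text. For example: the last value of the flagged measure dated after the intervention visit and within six months. A patient with no such value is missing, not unchanged.

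2. **Definition and model in agreement**, by one of two routes. Either reword the Secondary Outcomes item as yes/no, state the improvement criterion for each marker, and keep logistic regression; or keep the measured change and exempt this endpoint from the sentence that calls all outcomes dichotomous, naming the model that replaces logistic regression.

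3. **In either case, report the baseline-adjusted change for each marker in its own units**, with a pooled standardised ANCOVA, adjusted for baseline value and flagged marker, as a supporting analysis.

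The cost is wording and slightly more analysis work. The record abstraction is the same and the sample size does not change. The drawback is that a pooled standardised scale is less intuitive, which the marker-specific results offset. Enrolment and follow-up are under way according to the Trial status section, so the choice should be recorded before outcome data are analysed.

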#### Sample size

The target sample size is 190 (95 participants per group) to allow us to detect a 50% difference in the rate of occurrence of the primary outcome between the intervention and comparison group with 80% power and an alpha = 0.05. This assumes we observe a base rate of the outcome of 40% in the active comparator group, as we have observed in an unpublished analysis of data from a prior study, and 60% in the EMPATHy + Coached Care intervention group.

The sample size calculations do not account for loss to follow-up because the first primary outcome (development of a contextualized plan of care) is collected at the single intervention visit, and the second primary outcome (attainment of a concrete behavioral goal) is collected via telephone after a fairly short follow-up period (2 weeks) in patients who regularly access the clinic. Results from this pilot study will be used to estimate the rate of loss to follow-up for a definitive effectiveness trial.

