#### Medical visit

After the intervention visit, the patient will bring the list of questions into their regularly scheduled medical visit. With permission of the patient and the physician, the visit will be audio recorded using a portable digital recorder that the coach will place in the examination room and collect after the visit. Before beginning the recording, the coach will remind the patient that recording the visit is optional. If either the patient or the physician prefers that the visit not be recorded, the coach will not record the visit. In cases where the recording was not done, the study endpoints that require audio recordings will not be evaluated for that patient, but the remaining endpoints will be evaluated from the other data sources. No members of the study team will attend the medical visit, but will wait until after the visit to collect the recorder.

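### The 80% power for the contextualized-plan outcome holds only if almost no visit goes unrecorded, and the reason given for making no missing-data allowance does not cover refused recordings

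*Protocol article*

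**What the plan says.** Under Sample size, the protocol article states: "The target sample size is 190 (95 participants per group"), "with 80% power and an alpha = 0.05". The rates assumed are "a base rate of the outcome of 40% in the active comparator group" and "60% in the EMPATHy + Coached Care intervention group". It then says openly that nothing was added for missing outcomes: "The sample size calculations do not account for loss to follow-up because the first primary outcome", the contextualized plan, is captured on the day of coaching rather than later. For the second primary outcome, the behavioural goal, the reason is a short telephone follow-up among patients who use the clinic regularly.

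Two other sections bear on the first of these reasons. Under Outcome assessments, the contextualized plan of care is determined by coding an audio recording of the medical visit, and no other source is named. Under Medical visit, recording is optional for both parties: "If either the patient or the physician prefers that the visit not be recorded, the coach will not record the visit". The consequence is also fixed: "In cases where the recording was not done, the study endpoints that require audio recordings will not be evaluated for that patient". The same sentence keeps such patients in for all other endpoints.

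**The concern.** The sample-size section treats collection at the visit as if it secured the outcome. It does not: a patient can attend, be coached, see the doctor and still have no value for the first primary outcome because one of two people declined the recorder. The protocol foresees this and sets a rule for it in one section, then gives a reason in another that leaves it out.

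At stake is the power claim for one of the two primary outcomes. If 95 per group carried a margin, a few missing recordings would not matter. If 95 is the minimum, each unrecorded visit reduces power below the stated figure, and a reader of the sample-size section would not know it.

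**Working it through.** **Inputs.** From Sample size: p1 = 0.40, p2 = 0.60, difference 0.20, alpha 0.05, power 80%, n = 95 per group, no allowance. The protocol does not say whether alpha is two-sided. A two-sided test reproduces the figure and a one-sided test does not (77 per group), so two-sided is used. Normal quantiles are 1.960 and 0.842. The unrecorded share d is not in the documents; 10%, 20% and 30% are assumed, equal in both arms and unrelated to outcome.

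**Step 1: reproduce the plan's number.**

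- Sum of variances: 0.40 × 0.60 + 0.60 × 0.40 = 0.48.
- Unpooled: n = (1.960 + 0.842)² × 0.48 / 0.20² = 94.2, which rounds up to the planned 95.
- Pooled (average rate 0.50, so 2 × 0.50 × 0.50 = 0.50): n = (1.960 × √0.50 + 0.842 × √0.48)² / 0.20² = 96.9.

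The plan's 95 per group is therefore reproduced, and it is the number of patients with an outcome.

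**Step 2: power with complete data.** Φ is the standard normal distribution function.

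- Unpooled: Φ(0.20 / √(0.48/n) − 1.960). At n = 95: Φ(2.814 − 1.960) = 80.3%.
- Pooled: Φ([0.20 − 1.960 × √(0.50/n)] / √(0.48/n)). At n = 95: Φ(0.813) = 79.2%.
- Exact power of the chi-square test at n = 95: 79.3%.

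The stated 80% is right when every outcome is present. With 94 evaluable per group the two approximations give 79.9% and 78.8%, so there is no reserve.

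**Step 3: power for the contextualized-plan outcome with unrecorded visits.** Put n = 95 × (1 − d) into the same formulas.

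| Unrecorded share (assumed) | Evaluable per group | Unpooled | Pooled |
|---|---|---|---|
| 0% | 95 | 80.3% | 79.2% |
| 3% | 92.2 | 79.1% | 78.0% |
| 10% | 85.5 | 76.1% | 74.8% |
| 20% | 76 | 71.1% | 69.7% |
| 30% | 66.5 | 65.3% | 63.8% |

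Rounding 66.5 up to 67 patients gives 65.7% and 64.2%. In round terms power is about 75–76%, 70–71% and 64–66% at 10%, 20% and 30%. The exact chi-square test gives 76.0%, 68.2% and 63.3% at 85, 76 and 67 per group. Exact power moves unevenly with n, but the picture is the same.

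**Step 4: the 2-week goal outcome.** It comes from the follow-up call, and patients without a recording stay in for it. A refused recording leaves its n at 95. Only unreached calls would lower its power, and the loss would follow the same table with d as the unreached share.

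**The case against.** The strongest reply is that the protocol is candid. It says no allowance was made, says the pilot will be used to estimate loss for a definitive trial, and describes its purpose under Objectives and in the Discussion as estimating design parameters. The arithmetic is correct, and at 10% unrecorded the loss is only about 4 points of power. This stands as a limit on how serious the point is. It does not rescue the reason given, because the disclosure concerns loss to follow-up, whereas a refused recording is missing data at the visit itself, the place the section relies on for completeness. Pilot status does not remove the point either, since the Abstract and the sample-size section both make a power claim.

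Three stronger readings are tempting, and the documents do not support them.

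- A reader might infer that the design fails to reach 80% power. No refusal rate is given, so the shortfall is conditional; with complete recordings the stated figure reproduces.
- A reader might infer that both primary outcomes are affected. The Medical visit section retains unrecorded patients for every endpoint that does not need audio. For the goal outcome, the protocol argues from a 2-week interval and regular clinic users, and a second gift card follows the call. Whether that is optimistic is a judgement, not a contradiction.
- A reader might infer a biased comparison, because the patient is told that recording is optional after the arm-specific coaching session. For example, with a true rate of 40% in both arms, 10% versus 20% unrecorded and no plan in any unrecorded visit, the observed rates would be 0.40/0.90 = 44% and 0.40/0.80 = 50%. Both inputs are assumed and nothing in the documents points to either. The section also says the coach will remind the patient, which implies that permission was raised earlier, and the consent pages are not available to check.

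**Conclusion.** The point holds for the first primary outcome only. Its timing is not a valid reason for making no missing-data allowance, because the outcome depends on a recording that either party may refuse. The 190 is the evaluable number with no reserve, so 80% power for the contextualized plan of care requires that almost no visit goes unrecorded: by the pooled formula power is 78% at about 3% unrecorded. At an assumed 10%, 20% or 30% it is about 75–76%, 70–71% or 64–66%.

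These figures rest on two-sided alpha of 0.05, the protocol's 40% and 60%, and refusal that is equal between arms and unrelated to outcome. The defect is an unsupported assumption behind a stated design property. It is not an arithmetic error, a demonstrated loss of power or a demonstrated bias.

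**What to change.** In Sample size:

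1. Remove the timing of collection as the reason for making no allowance on the first primary outcome.
2. State that 190 is the number of patients with an evaluable outcome and that 80% power assumes complete outcomes.
3. Give the power for the contextualized-plan outcome at a stated assumed unrecorded share, for example 10%, 20% and 30%, with the values above.

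As a low-cost safeguard, settle recording permission with patient and physician before the allocation is revealed, where this is not already done, and keep the right to withdraw it at the visit. The Trial status section says enrolment was still under way, so this could protect patients not yet enrolled.

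Reporting unrecorded visits by arm and sensitivity analyses are commonly left to the full protocol or analysis plan and are not asked for here. Counting unrecorded visits as having no plan would not repair the power. At 20% unrecorded it turns 40% versus 60% into 0.80 × 40% = 32% versus 0.80 × 60% = 48%, with power of about 63% at 95 per group (unpooled formula).

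The cost is a few sentences, at most an earlier question, and a slightly less favourable stated power. No extra patients are needed.
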